##### Withdrawal management plan

2.6.4.3

In view of the possible loss of members, the “step-by-step retention” process is carefully designed. When a member fails to participate in the group activity for the first time, the peer educator sends a private letter in time, asks the reason in a friendly way, and expresses concern and encouragement; If the members were absent from the group activities for two consecutive times, the members of the steering group would conduct telephone interviews in person to understand the real thoughts and difficulties of the members, and try their best to provide help. If the member is confirmed to withdraw, the “personalized resource package” will be sent to the member according to their needs during the participation period, including targeted psychological adjustment materials, community support resources information, etc.

#### Regular health education

2.6.5

The regular health education (RHE) in the study is further elaborated as follows:

(1) Providers: It is delivered by uniformly trained medical staff, who possess professional knowledge in obstetrics, gynecology, and mental health to ensure the accuracy and effectiveness of the education.(2) Implementation Methods: The education is mainly conducted through telephone interviews and regular outpatient interviews. The frequency of telephone interviews is set at once every 3 days in the first 2 weeks, and then once a week for the remaining 4 weeks, each lasting 15–20 min. Regular outpatient interviews are scheduled once every 2 weeks, each lasting 30–40 min, allowing for more in-depth communication and assessment.(3) Specific Content: Postpartum health education includes guidance on postpartum recovery exercises, dietary nutrition (e.g., recommended foods for lactation and avoiding irritating foods), personal hygiene care, and management of common postpartum physical discomforts (e.g., abdominal pain, breast swelling). Mental health knowledge covers the causes, symptoms, and self-assessment methods of postpartum depression, as well as basic emotion regulation techniques (e.g., deep breathing, progressive muscle relaxation). Social support education involves helping participants identify available social support resources (e.g., family, friends, community support groups) and teaching them how to effectively seek and utilize these supports. Family member education aims to guide family members (especially spouses and parents) to recognize the importance of their role in the postpartum period, learn to provide emotional care and practical assistance to the parturient, and create a harmonious family environment conducive to her recovery.(4) Duration: The RHE intervention, same as IPE, lasts for 6 weeks to ensure continuous support for the parturient’s postpartum recovery.

#### Alternative therapeutic approaches

2.6.6

During the study period, participants are not prohibited from receiving treatments other than the specified intervention. In cases of aggravated symptoms requiring antidepressant therapy, participants will be referred to psychiatric hospitals, where antidepressants will be prescribed by specialist psychiatrists. All details of antidepressant use or other treatments (including type, dosage, administration frequency, duration, and initiation reasons) will be documented in the CRF. These data will be incorporated into the statistical analysis to account for potential confounding from concurrent treatments.

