What is inspiring, peer education services greatly benefit for recovery of people with mental health problems (6). Peer education is a structured intervention where individuals with lived experience of a specific condition (or similar life circumstances) provide support, share practical skills, and facilitate empowerment among those currently facing similar challenges (14). Peer educators can act as positive role for whom are currently experiencing mental distress by sharing real and useful skills they have acquired during their own experiences (9). It has to be notified that peer educators could not provide mental counsel but the information about depression, treatments, self-management and motivation for them to seek for needed professional services (10). But in other hand, peer educators may be more effective than mental health professionals at reducing stigma, enhancing attitudes toward mental health therapy because they share demographics with consumers (e.g., gender, age, income, etc.) and have personally experience involving mental illness (11). Moreover, peer education can help vulnerable groups that require mental health care but may feel excluded from the mainstream mental health system (12).

In this Internet age, a huge number of people can be offered low-threshold therapies online, regardless of time or location (15). A study shows that psychiatric patients use the Internet as frequently as the general population for engaging in online programs and accessing online health-related information (16). In addition, human support has repeatedly been shown to have a positive effect on effectiveness of and adherence to Internet-based interventions (17, 18). It has been shown in mental disorders that support provided by clinicians or coaches via telephone, email, and chat rooms could enhance adherence (19, 20). Consequently, online supportive program might be a promising approach to improve the accessibility, fairness, completeness, and quality of treatment for PPD population.

In the contemporary digital age, the relationship between peer education and internet—based interventions is intricate and mutually beneficial. Internet—based interventions offer a novel and far—reaching platform for the implementation and expansion of peer education.

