### Statistical analysis plan

2.10

The statistical analysis will be conducted by independent statisticians who will be blinded to group allocation and intervention methods. Before data analysis, the research group will draw up a statistical plan, including the required data and method of data processing. For Categorical data, we performed the Chi-square (x^2^) test for between-group differences. For continuous and normally distributed data, we performed Student’s *t*-test for between-group differences and paired t test for within-group differences. If data were distributed nonnormally, the Mann–Whitney U test for between-group differences and the Wilcoxon test for within-group differences would be used. The normally distributed data were expressed as the mean ± standard deviation. Nonnormally distributed data would be expressed as the median or interquartile range (IQR). For categorical variables, the X^2^ test will be used to examine the between-group differences, and percentages and frequencies will be presented to describe the effect size.

For longitudinal data analysis considering the repeated measurements at assessment nodes in this study, the Generalized Estimating Equations (GEE) model will be employed.

Fixed effects structure: It will include the group variable (experimental vs. control), time points (six assessment nodes as a categorical variable), and the interaction term between group and time points. Additionally, potential confounding variables (e.g., baseline characteristics that show imbalance between groups) will be incorporated into the model as covariates to adjust for their effects.

Correlation structure: Given the repeated measurements within individuals over time, the exchangeable (compound symmetry) correlation structure will be initially assumed, which posits that the correlation between any two measurements from the same individual is equal. Sensitivity analyses will be conducted using other correlation structures (e.g., autoregressive of order one, which assumes a higher correlation between measurements that are closer in time) to assess the robustness of the results. The working correlation matrix will be estimated based on the observed data during model fitting.

All clinical data analyses will be performed using SPSS V.22.0 software. Missing data will be handled using the multiple imputation method. A two-tailed test will be conducted, and a *p* < 0.05 will be considered statistically significant.

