### Safety

2.13

The steering group members and the assessment researchers will closely observe the psychological conditions of the peer educators and the participants during the whole course of trial. If an adverse event (AE) happened during intervention, it would be assessed and recorded in the case report form (CRF). The relevant adverse events may include deterioration of the depression, aggravating hopelessness, anxiety and somatic symptoms (et al., dizzy, pain). Serious adverse events include self-harm tendency, suicide attempt, and injury-infant behavior. Once a serious adverse event occurs, the participant will be immediately terminated from this trial and will be referred to a psychiatric clinic as soon as possible.

In addition to routine exclusion and monitoring criteria for suicidality, specific measures for symptom emergence during non-usual clinic hours are established. Participants will be provided with a 24/7 emergency hotline connected to on-call psychiatric professionals. Upon reporting suicidal symptoms, the on-call team will conduct immediate risk assessment via phone, dispatch emergency services if necessary, and coordinate with the participant’s primary caregiver for in-person supervision until professional intervention is available. Documentation of all interactions and follow-up actions will be maintained in the participant’s record.

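### Section 2.6.6 treats all concurrent treatment as confounding, including treatment started after randomisation because symptoms worsened; adjusting for the latter no longer estimates the effect of assignment

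*Protocol article*

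**What the plan says.** **Concurrent treatment.** Section 2.6.6 states that "participants are not prohibited from receiving treatments other than the specified intervention". It ties antidepressants to deterioration: "In cases of aggravated symptoms requiring antidepressant therapy, participants will be referred to psychiatric hospitals". Type, dose, frequency, duration and reason for starting go on the case report form, and then: "These data will be incorporated into the statistical analysis to account for potential confounding from concurrent treatments". No model, coding or time window is given.

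**Covariates.** Section 2.10 assigns the chi-square test to categorical data and a GEE model to the repeated measurements. For the GEE, "potential confounding variables (e.g., baseline characteristics that show imbalance between groups) will be incorporated into the model as covariates". Baseline imbalance is an example there, not a limit.

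**Safety events and missing data.** Section 2.13 says "Once a serious adverse event occurs, the participant will be immediately terminated from this trial". The safety item in section 2.6.1.2 ends only the intervention when suicidal tendencies or harmful behaviour appear. Section 2.10 says "Missing data will be handled using the multiple imputation method", with no exception.

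**The concern.** A confounder of a randomised comparison would have to influence which arm a participant is in. Treatment begun after allocation cannot do that. It can be a result of how the participant fares, and section 2.6.6 makes it one by naming worsening as the trigger for antidepressants. It may also depend on the arm. If IPE reduces worsening, fewer IPE participants will need an antidepressant. The Introduction also credits peer educators with giving "motivation for them to seek for needed professional services", which would act the other way.

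Conditioning on such a variable compares participants alike on something that the intervention may have changed. The result is no longer the effect of being assigned to IPE, which is the stated primary objective. Because 2.6.6 and the GEE covariate rule both speak of confounding, an analyst following the text could enter antidepressant use as a covariate and believe this was planned.

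The secondary issue is what happens to week-6 scores after a serious adverse event. If participation ends, those scores are missing, and imputation that ignored the deterioration would treat these participants like those who stayed.

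**Working it through.** The plan has no figure of its own on this point: it gives neither a rate of antidepressant use nor a rate of serious adverse events. What follows is illustration under stated assumptions.

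**1. Adjusting for treatment started after randomisation**

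Assumed model, 400,000 simulated patients per setting, 1:1 allocation (g = 1 for IPE):
- latent severity U ~ N(0,1); mid-trial severity M = U - 0.6·t·g + error with SD 0.5;
- probability of starting an antidepressant = logistic(-1.5 + 1.5·M);
- week-6 response if t·g - U + d·A + N(0,1) error - 1 > 0, where t is the IPE effect, d the drug effect and A antidepressant start.

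In the last two rows of the table, IPE has no direct effect, but its participants start the drug less often at the same severity (logistic(-1.5 + 1.5·U - δ·g), intercept for response -0.8). Response is regressed linearly on arm, without and then with A. The unadjusted difference is the effect of assignment.

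| IPE effect t | Drug effect d | Use RHE / IPE | Unadjusted | Adjusted | Shift (points) |
|---|---|---|---|---|---|
| 0 | 0 | 26.4% / 26.4% | 0.001 | 0.001 | 0 |
| 0.8 | 0 | 26.5% / 18.0% | 0.204 | 0.183 | -2.1 |
| 1.6 | 0 | 26.8% / 11.2% | 0.427 | 0.389 | -3.8 |
| 1.6 | 1 | 26.5% / 11.2% | 0.410 | 0.407 | -0.3 |
| 1.6 | 2 | 26.6% / 11.2% | 0.355 | 0.393 | +3.8 |
| none, δ = 0.5 | 0 | 25.3% / 19.0% | 0.000 | -0.015 | -1.5 |
| none, δ = 1.5 | 0 | 25.4% / 9.6% | 0.001 | -0.037 | -3.8 |

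Swapping the arm labels in the last two rows, so that IPE uses more, reverses the sign. The shift is therefore about -4 to +4 points in these settings. It is zero when IPE has no effect and use is equal, and nearly zero with a moderate drug effect.

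**2. Scores missing after a serious adverse event**

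Inputs from sections 2.4 and 2.9: 44 per arm, response 70% (IPE) and 28.3% (RHE). Assumed: x removals in IPE and y in RHE before week 6.
- Imputed at the arm's own rate, the difference stays 0.70 - 0.283 = 0.417.
- Counted as non-responders, it is 0.70·(44 - x)/44 - 0.283·(44 - y)/44.
- Shift from imputing = 0.70·x/44 - 0.283·y/44.

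| Removals | IPE only | RHE only | Both arms |
|---|---|---|---|
| 1 | +1.6 | -0.6 | +0.9 |
| 2 | +3.2 | -1.3 | +1.9 |
| 4 | +6.4 | -2.6 | +3.8 |

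These are worst cases, because HDRS17 is also collected at weeks 1, 2 and 4. Suppose the imputation uses the week-4 score, the correlation is 0.7, and the removed participant is 1.5 SD worse than the arm mean. The imputed response probability is 1 - Φ((0.7·1.5 - z)/√(1 - 0.49)), with z = 0.524 for 70% and -0.574 for 28.3%. This gives about 23% in IPE and 1% in RHE. Two removals per arm then add 2/44·0.23 = 1.0 point to IPE and 2/44·0.01 = 0.05 to RHE, a net shift of about 1.0 instead of 1.9.

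**The case against.** The strongest defence is that 2.6.6 does not say where the treatment data go. The chi-square test takes no covariates, the only covariates exemplified for the GEE are baseline ones, and 2.10 leaves the method of data processing to a statistical plan drawn up before analysis. This stands as far as it goes: a reader might infer that the week-6 primary test is already set to be adjusted and hence biased, and the document does not say so. It does not rescue the sentence, which commits to using these data and gives the wrong reason for it.

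Nor is all recorded treatment affected. Antidepressant users are not excluded at entry, and Table 1 records medication and therapies from the face-to-face interview and T0. Adjusting for treatment already in use is sound. That stands, and the fix keeps it.

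The route by which IPE raises help-seeking rests on a general remark in the Introduction; the weekly IPE activities in 2.6.1.2 list no such component. That route is possible rather than planned. The route through worsening symptoms is in 2.6.6 itself.

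On safety events, a reader might infer a written rule that clear failures are imputed as typical members of their arm, to the benefit of the better arm. No section says this. It needs 2.13 and 2.10 read together, 2.6.1.2 points the other way, earlier scores can inform the imputation, and removals in RHE alone would lower the difference. Making non-response the primary rule is also debatable: IPE participants have a weekly emotion rating and steering-group members in their chat groups, so events may be detected more often in that arm.

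**Conclusion.** The point holds in a limited form. Section 2.6.6 wrongly describes treatment started after randomisation as a source of confounding and leaves it open to be adjusted for, most readily in the GEE. An analysis that does so does not estimate the effect of assignment. The distortion is about -4 to +4 points on the week-6 risk difference in the settings tried, with roughly 25% to 27% use in RHE and 10% to 26% in IPE. Those rates and the drug effects are assumptions, the range is not a bound, and no single direction can be claimed. Multiple imputation is not biased in itself.

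The contradiction between 2.6.1.2 and 2.13 is a real secondary point. If scores do go missing, the effect of imputing at the arm's rate is at most about -2.6 to +6.4 points for 1 to 4 removals per affected arm, and less when earlier HDRS17 scores are in the imputation model.

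**What to change.** Replace the last sentence of 2.6.6 with wording to this effect: the primary analysis compares the randomised arms regardless of other treatment received; only variables measured at baseline, including treatment already in use then, may be covariates; treatment started after randomisation is described by arm and used only in a sensitivity analysis labelled as such. Limit the covariate sentence in 2.10 to baseline variables to match.

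Reconcile 2.6.1.2 and 2.13 on whether such an event ends the intervention or trial participation. If week-6 HDRS17 can be missing as a result, add to 2.10 a sensitivity analysis that counts those participants as non-responders, alongside the multiple imputation.

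The cost is a few sentences; the analysis changes need no new data. The small downside is that the primary estimate will include any benefit of other treatment, which the description by arm lets readers judge.

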### Quality control

2.7

The study is designed in accordance with the declaration of Helsinki (26). Researchers are divided by functions into recruitment, assessment, and treatment. All researchers will be trained before participating in this trial to ensure the consistency of assessment and treatment measures.

Researchers in charge of recruitment are a psychologist and a gynecologist, and they will develop standard operating procedures (SOPs) for better retention of subjects according to the recruiting situation.

Assessment researchers will be trained by psychiatrists on how to correctly use the HDRS17. Assessments at all-time points of one subject will be performed by the same researcher. Phone calls will be carried out not only for HDRS17 assessment, but also to improve compliance with the interventions and online self-report questionnaires. To keep the study procedures consistent across different researchers, SOPs will be developed and all researchers will be trained on the SOPs. All information will be recorded completely, standardly and in a timely manner on the CRF. We will randomly carry out self-inspection of CRFs to ensure completeness, accuracy and timeliness. Two researchers will transfer the data into a database and then cleaned and prepared the database.

Before onset of the trial, all selected steering group members will be organized to meet together, psychological expert will be invited to guide the content of mental health education, the management of the subjects, and the measures of emergency situations, so as to formulate management rules. After the start of the study, the steering group members should summarize the implementation of IPE in the steering WeChat group weekly, and revise the management rules if necessary to ensure the quality of IPE implementation.

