### Blinding

2.5

This study obeys the principle of blinding, and the separation of researchers, therapists and statisticians will be strictly implemented throughout the study. The efficacy evaluation during the observation is conducted by dedicated raters (research doctors, nurses, or postgraduates) who are unaware of the grouping status. For statistician blinding, the statisticians involved in data analysis are also kept blind to the grouping information. In case of emergency, the researcher could inform the doctor of the subject’s condition, so that the appropriate treatment could be taken. An emergency envelope with the subject’s random number and treatment plan will be prepared in advance, so that the doctor could open it in necessary.

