### Assessment

2.8

Assessments take place before the onset of the intervention period (T0), 1 week (T1), 2 weeks (T2), 4 weeks (T3) after the intervention has started, and at the end of the intervention (6 weeks after start of the intervention; T4). Follow-up will take place at 12 weeks after the end of the intervention (T5) (Table 1). Each assessment consists of an online questionnaire and a telephone interview. Except HDRS17, the EPDS, WHOQOL and SMCDS are self-report scales, which will be filled out online at T1-T5. The access of online questionnaires will be sent to subjects by researchers in charge of assessment, at the assessment nodes after inclusion. HDRS17 will be assessed by researchers through telephone interview with subjects.

**Table 1 tab1:** Overview of assessment points and measurements used.

	Online screening	Face-to-face interview	T0	T1	T2	T3	T4	T5
			-7 ~ 0d	1w ± 3d	2w ± 3d	4w ± 3d	6w ± 3d	12w ± 3d
In−/exclusion criteria	×							
Witten consent form		×						
Sociodemographic information		×						
Regular health education			×	×	×	×	×	
Internet-based peer education			×	×	×	×	×	
Edinburgh Postpartum Depression Scale			×	×	×	×	×	×
17-item Hamilton Depression Rating Scale			×	×	×	×	×	×
World Health Organization Quality of Life Scale Brief			×	×	×	×	×	×
Self-Efficacy to Manage Chronic Disease Scale			×	×	×	×	×	×
Medical history, medication, therapies		×	×	×	×	×	×	×
Adverse event		×	×	×	×	×	×	×
Assessment of adherence		×	×	×	×	×	×	×
Completion assessment		×	×	×	×	×	×	×
Review by investigator		×	×	×	×	×	×	×

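### The calls that score the HDRS17 are also meant to improve compliance with the interventions, which exposes raters described as blind to learning the patient's arm

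*Protocol article*

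**What the plan says.** Section 2.5 (Blinding) assigns efficacy evaluation to "dedicated raters (research doctors, nurses, or postgraduates) who are unaware of the grouping status" and promises that "the separation of researchers, therapists and statisticians will be strictly implemented throughout the study". Section 2.12 (Secondary outcome) repeats that the staff who collect the scales do not know the allocation.

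Section 2.8 (Assessment) fixes how the primary measure is obtained: "HDRS17 will be assessed by researchers through telephone interview with subjects". Section 2.11 turns it into a responder status at week 6, with a cut at 50% improvement from baseline.

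Section 2.7 (Quality control) says "Researchers are divided by functions into recruitment, assessment, and treatment". Its paragraph on the assessment researchers then says "Assessments at all-time points of one subject will be performed by the same researcher", followed directly by "Phone calls will be carried out not only for HDRS17 assessment, but also to improve compliance with the interventions and online self-report questionnaires".

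Section 2.13 (Safety) says that, together with the steering group, "the assessment researchers will closely observe the psychological conditions of the peer educators and the participants" throughout the trial.

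Sections 2.1 and 2.6.1 give RHE to both arms and IPE to the intervention arm only. Peer educators therefore work only in that arm.

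**The concern.** Patients know their arm, and section 3.1 accepts this. It names patients as the unblinded party and says nothing of raters. A rater who does not know the arm is therefore the plan's safeguard against observer bias in the primary outcome. The outcome is an interviewer-scored scale cut at a threshold, so a small scoring shift near the line changes a patient's status.

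The two arms differ in what there is to comply with. RHE consists of telephone and outpatient interviews (2.6.5). IPE adds WeChat groups, posted content and a weekly group video chat (2.6.1.2). If the rating call also covers compliance, the conversation turns to the one thing the rater is meant not to learn. Because the same rater continues with the patient, a disclosure at week 1 is still with the rater at week 6.

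**Working it through.** **Text comparison.** The conflict itself rests on no figure in the plan, so it is checked by setting the sections side by side.

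| Point | Section | Content |
|---|---|---|
| Safeguard | 2.5, 2.12 | Raters and scale collectors do not know the group |
| Primary measure | 2.8, 2.11 | HDRS17 by telephone; responder status at week 6 |
| Second use of the calls | 2.7 | Compliance with the interventions and the online questionnaires |
| Continuity | 2.7 | One rater per patient at all time points |
| Arm difference | 2.1, 2.6.1 | Only one arm has the peer programme |
| Further contact | 2.13 | Assessment researchers among those observing peer educators |

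1. Reminders about the online questionnaires are harmless, since both arms complete them.
2. Compliance with the interventions differs by arm, so discussing it on a rating call opens a route to disclosure.
3. Single-rater continuity makes any disclosure last until the primary time point.
4. The observation duty in 2.13 brings raters near IPE delivery. It does not alone identify a given participant's arm: 2.6.1.2 lists the WeChat group members as steering group, peer educators and participants, not assessors.

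**Illustration of size.** Inputs from the plan (2.9): a 28.3% response under health education, and 38 per arm before or 44 per arm after the dropout allowance. Assumed inputs: a second base rate of 40%, no true effect, and a share *s* of IPE non-responders scored over the line because the rater knows the arm, with no shift in the RHE arm.

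Apparent IPE response = *p* + *s*(1 − *p*):

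- *p* = 0.283, *s* = 0.10: 0.283 + 0.10 × 0.717 = 0.355, a difference of 7.2 points.
- *p* = 0.283, *s* = 0.20: 0.283 + 0.20 × 0.717 = 0.426, a difference of 14.3 points.
- *p* = 0.40, *s* = 0.10: 0.40 + 0.10 × 0.60 = 0.46, a difference of 6.0 points.
- *p* = 0.40, *s* = 0.20: 0.40 + 0.20 × 0.60 = 0.52, a difference of 12.0 points.

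The rejection probability sums the product of the two binomial probabilities over every pair of responder counts for which the uncorrected chi-square is significant at two-sided 5%:

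| Base response | Share moved | 38 per arm | 44 per arm |
|---|---|---|---|
| 28.3% | 0 | 5.2% | 5.3% |
| 28.3% | 10% | 10.4% | 11.7% |
| 28.3% | 20% | 25.6% | 30.4% |
| 40% | 0 | 4.9% | 5.2% |
| 40% | 10% | 8.1% | 8.6% |
| 40% | 20% | 18.3% | 19.3% |

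Across both sample sizes the range is 8–12% for a 10% shift and 18–30% for a 20% shift.

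**The case against.** The sentence in 2.7 is passive and names no caller. Both arms receive RHE, largely by telephone, so a generic prompt to keep up with the programme could be given without knowing the arm. The same section promises SOPs and training, and it separates assessment from treatment. All of this stands. A reader might infer that the call cannot be made without knowing the arm, or that the blinding is lost. The documents support neither. What remains is that the sentence sits in the assessment researchers' paragraph, describes the HDRS17 calls themselves, and assigns the compliance part to no one else.

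The sentence in 2.13 can be read as dividing the work, with the steering group watching the peer educators and the assessors watching participants. A reader might also infer that observing peer educators shows raters who is in IPE. That would need observation inside the WeChat groups, which the protocol does not state. This part is therefore secondary.

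A blind rater would not remove all bias. The HDRS17 is scored from the answers of patients who know their arm, and section 3.1 acknowledges expectation effects. The fix deals with observer bias only.

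The bias sizes in the illustration are assumptions, and they run in one direction. They show sensitivity and do not predict what happened in this trial.

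**Conclusion.** The point holds as an exposure created by the stated text. Sections 2.5 and 2.12 promise raters who do not know the group, while 2.7 gives the rating calls a purpose that invites disclosure and keeps the same rater through week 6. Section 2.13 adds a weaker exposure. The wording permits unblinding but does not require it or show that it will happen.

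The size is unknown. Under the assumed shifts, an apparent advantage of 6 to 14 points could arise with no true effect, and the false-positive rate could rise from about 5% to between 8% and 30%. This merits correction because the primary outcome depends on the rater and the remedy is cheap. Confidence is medium, because the caller is not named and SOPs may already separate the tasks.

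**What to change.** - **Section 2.7:** limit the rater's call to the HDRS17 interview and reminders for the online questionnaires, opening with a request not to mention the education programme. Assign all contact about compliance with the interventions to the treatment researchers, a function this section already separates.
- **Section 2.13:** state that observation of the peer educators is done by the steering group or other staff who do not rate the HDRS17, so that no safety observation is lost.
- **Optional:** have the rater record a guess of the arm at T4.
- **Ratings already made:** recruitment began in July 2023, so a change of wording cannot protect earlier scores. Report who made the compliance calls and, if raters did, qualify the blinding claim.

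The cost is a revision of the SOP wording, separate compliance calls by existing staff, and one extra CRF item if the guess is recorded.
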